## Abstract

**Background:**

Community Acquired Pneumonia (CAP) is the leading cause of childhood morbidity and mortality worldwide including India. Many of these deaths can be averted by creating awareness in community about early symptoms of CAP and by ensuring availability of round the clock, quality health care.

The objective was to assess the effectiveness of an innovative package of orienting doctors and community health workers about community perceptions on CAP barriers to qualified health care seeking, plus infrastructural strengthening by (i) providing “Pneumonia Drug Kit” (PDK) (ii) establishing “Pneumonia Management Corner” (PMC) at additional primary health center (PHCs) and (iii) “Pneumonia Management Unit” (PMU) at Community health center (CHCs) along with one of 4 different behavior change communication interventions**:**Organizing Childhood Pneumonia Awareness Sessions (PAS) for caregivers of children < 5 years of age during a routine immunization day at PHCs and CHCs by Auxillary Nurse Midwives (ANM)Organizing PAS on Village Health and Nutrition Day only once a month in villages by Accredited Social Health Activist (ASHA)Combination of both Interventions 1 & 2Usual Careas measured by number of clinical pneumonia cases-treated by ANM/doctors with PDK or treated at either PMC or PMU.

**Methods:**

Prospective community based open labeled behavioral trial (2 by 2 factorial design) conducted in 8 rural blocks of Lucknow district. Community survey will be done by multistage cluster sampling to collect information on changes in types of health care providers’ service utilization for ARI/CAP pre and post intervention.

**Discussion:**

CAP is one of the leading killers of childhood deaths worldwide. Studies have reported that recognition of pneumonia and its danger signs is poor among caregivers. The proposed study will assess effectiveness of various communication strategies for improving childhood pneumonia case management interventions at mother/community level, health worker and health center level. The project will generate demand and improve supply of quality of care of CAP and thus result in reduced mortality in Lucknow district. Since the work will be done in partnership with government, it can be scaled up.

**Trial registration:**

This study has been registered retrospectively in the AEARCT Registry and the registration number is: AEARCTR-0003137.

**Electronic supplementary material:**

The online version of this article (10.1186/s12887-018-1250-4) contains supplementary material, which is available to authorized users.

## Background

Pneumonia, the leading cause of childhood morbidity and mortality worldwide, is responsible for deaths of more than 2 million children annually [1]. Among these, two-third deaths are concentrated in just 10 developing countries, India being one of them. It is estimated that 408,000 children less than 5 years die due to clinical pneumonia in India [2]. Many of these deaths can be averted by creating awareness of the community about early signs of pneumonia and by ensuring availability of round the clock, quality health care.

After extensive formative research on childhood pneumonia in Uttar Pradesh and Bihar (14 districts), we found that pneumonia related morbidity and mortality can be averted if the following barriers are addressed: (a) delay in symptom recognition (b) delay in timely and qualified health care seeking (c) distrust of the community on the available public health services [3]. Thereafter, we developed and validated text, audio, video messages to address these barriers [4]. Specifically, messages were developed on (a) symptom recognition (b) where and when to seek treatment (c) how to approach a care provider and negotiate for quality of care (d) risk vulnerability perception. The proposed project aims to leverage the extensive work done and conduct operations research to address these three barriers to health care seeking through innovative community based approaches using messages developed by us as well as by strengthening the existing public health system.

At present, only 70.8% rural children seek care for symptoms of acute respiratory infections [5]. Our hypothesis is that strengthening of public health system to provide sustainable quality care for cases of childhood pneumonia (CAP) followed by strategic dissemination of validated messages to community by public health grass-root  workers may improve care seeking behavior for CAP within 12 months from qualified public health care providers. Goal of this project was to enhance early recognition and care seeking for CAP from public health system by ensuring empowerment of community and care providers for delivery of round the clock, quality-care.

## Methods/design

### Study aim

Our primary aim is to assess the effectiveness of an innovative package of orienting doctors and community health workers (CHW) about community perceptions on CAP barriers to qualified health care seeking plus infrastructural strengthening by (i) providing “Pneumonia Drug Kit” (PDK) (ii) establishing “Pneumonia Management Corner” (PMC) at additional primary health center (APHC) and (iii) “Pneumonia Management Unit” (PMU) at Community health center (CHC) *ALONG* with one of the 4 different behavior change communication (BCC) interventions:Intervention 1: Organizing Childhood Pneumonia Awareness Sessions (PAS) for caregivers of children < 5 years of age during a routine immunization day, using self-developed and validated Information, Education and Communication (IEC) materials, in PHCs and CHC monthly, conducted by a trained Auxillary Nurse Midwife (ANM) and project facilitators.Intervention 2: Organizing PAS on Village Health and Nutrition Day (V.H.N.D.) once a month by the Accredited Social Health Activist (ASHA) trained to conduct such sessionsIntervention 3: Combination of Both Intervention 1& 2Intervention 4: Usual Care

Outcome measure will be number of CAP treated by ANMs/doctors with medicines from PDK or treated at either PMC or PMU in interventions given by ANMs/ASHA workers.

Our second objective is to ascertain change, if any, in the types of health care providers’ service utilization for Acute Respiratory Illness (ARI)/CAP in last 12 months in children less than 5 years pre and post intervention.

Outcome measure will be number of ARI/CAP Treated by ANMs/doctors by various health care providers in the past 12 months in interventions given by ANMs/ASHA workers.

### Study setting & participants

This study will be conducted in rural areas of Lucknow district, which is the capital of state of Uttar Pradesh in North India. Lucknow district has a population of 4,589,838, of which 33.79% are rural [6]. Here, there are 8 rural administrative blocks. Public health system for each of these blocks comprises of at least one (and in one block two) community health center (CHC) with outpatient care by doctors including pediatricians and 30 inpatient beds. Under each CHC are additional primary health centers (PHCs) for approximately 100,000 population with outpatient facilities and 4 beds. The lowest level of care is through a sub-center with an ANM. There is one subcenter for about 5 villages. Existing health infrastructure in Lucknow block at the initiation of the project is given in Table 1.

**Table 1 Tab1:** Health Infrastructure of Lucknow Distric**t**

Health Infrastructure of Lucknow District	Number
Blocks	08
Community Health Centre (CHC)	09^a^
Total Sub Centre (SC)	345
Functional SC	331
Non Functional SC	14
Additional Primary Health Centre (APHC)	28
Accredited Social Health Activist (ASHA)	1246
Auxillary Nurse Midwife (ANM)	331
Super specialty hospitals	03
District combined hospitals	04
District hospitals	03
District Women hospitals	02
Number of AYUSH hospital/dispensary	78
Number of Ayurvedic hospital/dispensary	49
Number of homeopath hospital/dispensary	29

^a^BKT Block has two CHCs. Other 7 blocks have one CHC each

In the study, target population will be caregivers within the family of children < 5 years who were residing in the study area. No caregiver with a child < 5 years will be excluded.

### Study design

A Community Based Open Labeled Behavioral Trial conducted in 2 by 2 factorial design (Table 2) and geographic distribution of these areas is given (Fig. 1). Two blocks, proportionately equal in terms of number of ASHA workers (roughly equal to be number of villages) have been purposively paired and then randomly assigned to an interventional arm. Health infrastructure in each intervention arm is given in Fig. 2.

**Table 2 Tab2:** Design of the project

		PAS at APHCs/CHCs	
		Yes	No
PAS on VHND PLUSVillage IEC	No	Gosaiganj Block and Mall Block (Intervention1)	Bakshi Ka Talaab Block and Chinhat Block (Intervention 4)
	Yes	Malihabad Block and Mohanlalganj Block (Intervention3)	Sarojininagar Block and Kakori Block (Intervention2)

*Abbreviations PAS* Pneumonia Awareness Session, *VHND* Village Health and Nutrition Day, *IEC* information education communication, *PHC* Primary Health Centre, *APHC* Additional Primary Health Centre, *CHC* Community Health Center

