##### Behavior change communication for demand generation for pneumonia management by the community

To ensure optimal utilization of augmented health facilities by measures mentioned above, a behavior change in the community will be needed, with respect to management of CAP. This behavior change can be brought about by various BCC strategies that utilize the messages developed by us. Effective behavior change is likely to result in demand generation for better quality of care from the public health sector for CAP by the community.

To identify the most effective BCC strategy, PAS will be conducted for caregivers who voluntarily bring their children for immunization either at the PHC/CHC or on VHND at the *anganwadi* center (AWC) as are likely to be receptive to health education messages. There will also be diffusion of messages in the community. PAS will bridge the gap and build confidence of the community in the public health system and services. We will be able to identify what is the minimum effective package of services that will result in optimal utilization of augmented public health facilities.

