Univariate distribution of baseline and outcome variables would be assessed by frequency counts. Outliers will be identified, reported and excluded from analysis if required. They would be compared between interventions using chi square test for categorical and Student’s t test and ANOVA for continuous variables. A *p* value of < 0.05 will be taken as statistically significant, using a two tailed distribution. Adherence to the intervention across each arm will be calculated and compared across the three arms (as one was a control arm). Good intervention is defined as > 75% adherence to the sessions in the duration of the project. Primary outcomes will be number of PDK kits distributed to children plus the number of children treated by government functionaries for acute respiratory infection (ARI) or pneumonia without PDK, using medicines available at the health facility in interventions given by ANMs/ASHA workers. If we find that the diagnosis of children being treated is not mentioned, then we fill this missing information by extrapolation from data where diagnosis is given for the same month and within the intervention arm, assuming that there would be similar proportion of cases with this diagnosis. We will compute the difference in the proportion of ARI/pneumonia treated in each intervention arm when compared to control arm in the intention to treat analysis. For the secondary outcome, we will compare the proportion of cases with ARI/pneumonia treated by government providers as their first choice in interventions given by ANMs/ASHA workers, as an intention to treat analysis. In the per-protocol analysis we will compare the proportion of cases with ARI/pneumonia treated by government providers as their first choice in interventions given by ANMs/ASHAs from those households which have participated in the baseline as well end line survey using paired t-test. As a sub-analysis, we will compare the mean, median and interquartile range of out of pocket expenditure for ARI/pneumonia in the baseline and end line survey within each arm. As a comparator, we will do similar analysis for cases who have suffered from diarrhea to assess whether changes in spending were a function of time or because of care seeking from government providers, which is most inexpensive.

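### Four purposive pairs of blocks, not eight blocks, were randomised, one pair per arm, so no planned two-sided contrast can reach p < 0.05 by re-randomisation

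*Protocol article*

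**What the plan says.** Study setting & participants gives the number of available units: "Here, there are 8 rural administrative blocks". Study design describes a trial "conducted in 2 by 2 factorial design" and explains the allocation: "Two blocks, proportionately equal in terms of number of ASHA workers" "have been purposively paired and then randomly assigned to an interventional arm". Table 2 shows the result, two blocks in each of the four cells, for example "Gosaiganj Block and Mall Block (Intervention1").

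Data management & analysis plan sets the decision rule: a p value below 0.05 "will be taken as statistically significant, using a two tailed distribution". It also names the main comparison: "We will compute the difference in the proportion of ARI/pneumonia treated in each intervention arm when compared to control arm". The tests listed there are chi-square, t test, ANOVA and tests of proportion. No block or pair term is mentioned.

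The intended use is ambitious. The rationale for the communication interventions says "We will be able to identify what is the minimum effective package of services". Ethics and research governance says the best strategy will be found and extended to the whole district, and Post intervention phase looks to the whole state.

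**The concern.** The unit that was randomised is the pair. With four pairs and four arms, each arm is a single random draw. Any difference between pairs in access, staffing, case load or record keeping appears as a difference between arms, and the design has no second pair per arm to show how large such differences are by chance. The two blocks in an arm are not two independent draws, because they were put together on purpose and moved together.

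At stake is the choice of strategy for scale-up. A p value below 0.05 from children or households would look like evidence for one communication strategy, when it might reflect only which pair of blocks was drawn for that arm.

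**Working it through.** The article states no power or precision figure, so there is none to reproduce. The check counts the allocations that the randomisation could have produced.

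**Inputs.** Eight blocks (Study setting & participants); four pairs, one per arm (Study design, Table 2); two-sided 0.05 and arm-against-control contrasts (Data management & analysis plan).

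**Allocations.** Pairs: 4! = 24. Single blocks, two per arm: 8!/(2!)^4 = 2,520.

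**Smallest two-sided p under the null that no arm has any effect.** The most extreme result and its mirror image both count, hence the 2 in each numerator.
- Arm against control, pairs: 4 × 3 = 12 ordered choices of the two pairs, so 2/12 = 0.167.
- Main effect or interaction, pairs: C(4,2) = 6 splits, so 2/6 = 0.333.
- Main effect, single blocks: C(8,4) = 70 splits, so 2/70 = 0.029.
- Arm against control, single blocks: C(8,2) × C(6,2) = 28 × 15 = 420, so 2/420 = 0.0048.
- An overall four-arm test on arm totals with pairs: the statistic does not change when pairs are relabelled, so p = 1.

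**Narrower nulls.** If only the arms being compared are re-randomised, arm against control has a floor of 2/2 = 1.0 with pairs and 2/C(4,2) = 2/6 = 0.333 with single blocks. If the other factor is allowed an effect and held fixed, a main effect has a floor of 2/(2 × 2) = 0.5 with pairs and 2/(6 × 6) = 0.056 with single blocks.

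**Other matched layouts of the same eight blocks.** Splitting each pair across one factor gives 2/2^4 = 0.125. Two matched sets of four, one block per arm, give 2/36 = 0.056 for a main effect. Eight blocks are few under any scheme.

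**Precision, conditional on an assumption.** Let block outcomes have variance s² and within-pair correlation r, which the article does not give. The variance of a main effect, averaged over allocations, is:
- bound pairs: s²(1 + r)/2
- single blocks: s²(1 − r/7)/2, because two given blocks have an expected sign product of −1/7 in a random 4:4 split.

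The SE ratio is √[(1 + r)/(1 − r/7)]:
- r = 0.3: √(1.3/0.957) = 1.17
- r = 0.5: √(1.5/0.929) = 1.27
- r = 0.7: √(1.7/0.9) = 1.37
- r = −0.3: √(0.7/1.043) = 0.82

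**The case against.** The best counter-argument concerns what the pairing was for. A reader might infer that matching was used backwards, with like blocks placed together instead of apart. That is the more natural reading, but the phrase can also mean that pairs were built so that arms carry similar ASHA totals. Fig. 2, which might settle it, is not shown. Table 1's footnote gives one block two CHCs and the rest one each, and Table 2 pairs that block with a one-CHC block, which fits compensating pairs about as well as like pairs. Under that reading r could be negative and the protocol's scheme could be the more precise one (0.82 at r = −0.3). This objection stands, and the precision point is conditional for that reason. The unit count, the confounding and the p floors do not depend on it.

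A reader might also infer that no randomisation-based test can reach 0.05. That is too strong: a prespecified full ordering of the four arms can reach 1/24 = 0.042, although its usual doubled two-sided value is 2/24 = 0.083. The article plans no such test. Nor should 1.0 be quoted as the only floor for arm against control, since over the full randomisation it is 0.167.

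Baseline and endline surveys allow change from baseline for provider preference, which can remove stable differences between pairs. That helps the estimate for that outcome but adds no randomised units.

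Finally, the article plans no randomisation test, so its stated tests can return p < 0.05. That is true, but they do so by ignoring the unit that was randomised.

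**Conclusion.** The point holds in a limited form. Four units were randomised, one per arm, and arm is fully confounded with pair. Every two-sided contrast that the article plans has a re-randomisation floor above its own 0.05 threshold: 0.167 for an arm against control and 0.333 for a factorial main effect. These floors follow from counting and need no assumption about outcomes or about why the blocks were paired.

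Pairing is not the only cause, because eight blocks would be tight in any layout. It does matter, however: the same blocks drawn singly bring a main effect to 0.029 under the null of no effect in any arm. The SE inflation of about 1.17 to 1.37 is a secondary point. It needs alike pairs, an ASHA number that predicts outcome, and r between 0.3 and 0.7; none of these is established by the document.

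**What to change.** **If roll-out has not begun:** in Study design, randomise the eight blocks singly, two per arm, and test the two main effects by permutation over the allowed allocations. If allocations are restricted for ASHA balance, more than 40 of the 70 main-effect splits must remain, equally likely, because 2/40 is exactly 0.05. State the null being tested: the 0.029 floor assumes no effect in any arm, and holding the other factor fixed raises it to 0.056. The cost is one new draw and the loss of the administrative grouping; no blocks, staff or patients are added.

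**If the Table 2 allocation stands**, as the wording of Study design suggests:
- State that four purposive pairs were randomised, one per arm, and that arm is confounded with pair. Say also what the pairing on ASHA number was meant to achieve.
- Present arm differences as estimates, as change from baseline where the surveys allow, without a p < 0.05 claim.
- Soften the statements that the minimum effective package and the most effective strategy will be identified.
- Treat any adjustment for ASHA number as exploratory. If paired blocks really are alike, that covariate is nearly aliased with arm.

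This costs wording only, and the strength of the conclusion falls to what four draws can support.

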**Fig. 1 Fig1:**
[figure not shown]
Block wise distribution of four project interventions

**Fig. 2 Fig2:**
[figure not shown]
Distribution of rural health infrastructure across 8 blocks and their allocation to project intervention arms. `community orientation` CHC: Community Health Center; APHC: Additional Primary Health Centre; SC: Subcentre; ANMs: Auxiliary Nurse Midwifery; ASHA: Accredited Social Health Activist

#### Rationale for intervention

##### Establishment of PMU, PMC, PDK plus community orientation of doctors, ANMs and ASHA workers

Strengthening the capacity CHCs, PHCs and SCs for the management of CAP will result in better delivery of pneumonia specific care; this will build community’s trust in the public health system.

##### Behavior change communication for demand generation for pneumonia management by the community

To ensure optimal utilization of augmented health facilities by measures mentioned above, a behavior change in the community will be needed, with respect to management of CAP. This behavior change can be brought about by various BCC strategies that utilize the messages developed by us. Effective behavior change is likely to result in demand generation for better quality of care from the public health sector for CAP by the community.

To identify the most effective BCC strategy, PAS will be conducted for caregivers who voluntarily bring their children for immunization either at the PHC/CHC or on VHND at the *anganwadi* center (AWC) as are likely to be receptive to health education messages. There will also be diffusion of messages in the community. PAS will bridge the gap and build confidence of the community in the public health system and services. We will be able to identify what is the minimum effective package of services that will result in optimal utilization of augmented public health facilities.

#### Trainings

##### Orientation of doctors, ANMs and on ASHA workers on prevalent community pneumonia management practices

The participants will be given the innovative `community orientation` to CAP using vignettes of real life cases of CAP, informed about community barriers to case management and their perceptions of health facilities. Thereafter, they will be shown the messages developed and told about the rationale behind each. They will be told about infrastructural strengthening, namely, PDK, PMC, PMU (Table 3). Additional training will be given to the care providers separately as given below.

**Table 3 Tab3:** Framework for Infrastructural Strengthening

Site	Infrastructural strengthening and purpose
Subcentre/PHC/CHC	PDK containing dispersible pediatric amoxicillin tablets (250 mg) PLUS instruction card will be provided by the project. Ten doses of amoxicillin (for a maximum of 5 days) will be kept in transparent envelop with *green sticker* for children below between 1 and 12 months and * yellow sticker* for children between 12 and 59 months. Each envelope will also have 4 tablets of paracetemol (500 mg). Within each envelope will have a small card with instructions for use of medicines on one side, and how to monitor a child with clinical pneumonia for improvement and deterioration on the other side will be kept. Instructions will be in Hindi.
APHC	PMC to treat pneumonia with fast breathing and stabilize &refer pneumonia with lower chest in-drawing with hypoxia (pulse-oximetry< 92%) and severe pneumonia. Project to provide: PDK, Pulse oximeter, spacer with baby mask, salbutamol inhaler. State Government Supply: Earmark ONE existing bed as *pediatric pneumonia bed,* storage facility for drugs, equipment and patient records and common facilities like 24X7 doctor-nurse; Injectibles: ampicillin, gentamycin, ceftrioxone, corticosteroid; Oral: antipyretics, co-trimoxazole; oxygen, face mask, suction machine and mucus extractors, laryngoscope, endotracheal-tube, ambu-bag, thermometer, pediatric blood pressure instrument.
CHC	PMU to treat pneumonia with fast breathing and lower chest in-drawing and admit pneumonia with hypoxia (pulse-oximetry< 92%) and severe pneumonia. Project to provide: PDK, Pulse oximeter, spacer with baby mask, salbutamol inhaler. State Government Supply: Earmark TWO existing beds as *pediatric pneumonia beds,* storage facility for drugs, equipment and patient records and common facilities like 24X7 doctor-nurse; Injectibles: ampicillin, gentamycin, ceftrioxone, corticosteroid and vasopressors (dopamine), calcium, potassium, intravenous fluids like dextrose saline, Ringer Lactate; oral: antipyretics, co-trimoxazole; bronchodilators; oxygen, face mask,suction machine and mucus extractors, laryngoscope, endotracheal-tube, ambu-bag, thermometer, pediatric blood pressure instrument, nebulizer with nebulizer solutions of salbutamol, epinephrine and steroid, intravenous cannula, venous cut-open set, heater/warm air blowers for winter months.

*Abbreviations APHC* Additional Primary Health Centre, *PHC* Primary Health Centre, *CHC* Community Health Center, *PDK* Pneumonia Drug Kit, *PMC* Pneumonia Management Corner, *PMU* Pneumonia Management Unit

A brief refresher course on ARI module of F-IMNCI will be organized for doctors. Medical management of CAP in paediatric ward of a tertiary care teaching hospital will be demonstrated. Doctors will also be trained to record clinical data of CAP patients in simple to use case sheet prepared for the project. Training will be done in KGMU by F-IMNCI trained faculty.

A brief refresher course on ARI module will be also be organized for the ANMs in their respective CHCs. Investigators and faculty trained in F-IMNCI will impart training. ANMs will be trained to use drugs from PDK in the villages and SC and document it. They will also be trained to refer CAP with lower chest in-drawing or severe pneumonia by calling ambulance services by dialing 102/108. ANMs will be trained to conduct PAS using (a) case-stories (in video/text formats) (b) messages for early recognition of pneumonia, when and where to seek care, risk perception of delayed treatment or treatment from unqualified provider and also for recognition of the danger signs of pneumonia through the self-developed posters, audio and video messages as well as (c) inform the community about infrastructural strengthening, PDK, PMC, PMU and (d) respond to queries.

ASHA workers will be provided the same training capsule as for the ANMs with the exception that (a) on finding a suspected case of CAP, ASHA workers will either contact the local ANM for immediate urgent case confirmation and treatment or expedite referral by calling ambulance services by dialing 102/108 (b) they will not dispense drugs from PDK (c) They will conduct PAS sessions in VHND using only with the cases stories and messages in text (poster) format. Project Staff at CHC will train them in batches. Table 3 provides the framework of infrastructural strengthening.

